**Table 1 Tab1:** **Intervention domains and sample text messages**

Domain	Sample text message
Improving a sense of social support	Stay strong. The clinic cares about you.
Ameliorating negative affect	Everyone feels sad sometimes. Remember you can talk to your provider about depression.
Bolstering positive affect and coping	Smile, breathe, and go slowly.
Fostering empowerment	Be active in your health care. Keep your scheduled appointments.
Supporting healthy behaviors and health maintenance	Invest in your health. Remember to get your Pap smear.
Emphasizing the value of antiretroviral adherence and persistence	Taking meds? They help, even if you can’t tell they are working.

Additional formative work included a pilot phase to test technical and administrative aspects of field operations, as well as the acceptability of intervention text messages. We obtained feedback on one month of messages from participants enrolled in an open-phase pilot (n = 10) to further refine intervention content. These pilot participants then entered an extension phase in which main study procedures and instruments were tested with this group, so as to resolve any technical glitches prior to deployment with main study participants. Pilot participant data will not be analyzed with that of randomized study participants.

Intervention messages are divided into three response types. Type 1 is a message that asks for no response (one-way). Type 2 asks participants if they found the message helpful (two-way). Type 3 asks participants if they would like more information on a topic and if they answer yes, they receive a message with additional information (three-way). Each domain has messages from each response type, and domain-specific messages are randomly ordered over the twelve-month intervention period. Intervention group participants receive at least one Type 2 or 3 message per week because we track responses to estimate the amount of intervention participants receive. Participants can choose morning, afternoon, or evening times to receive intervention messages.

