**Table 2 Tab2:** **Use of clinic and study data sources to ascertain study outcomes**

	Retained in C4C study	Lost to C4C study
Retained in care	Viral load and appointment data available from EMR, outside clinic records, and, when necessary, study phlebotomy	Viral load and appointment data available from EMR and (if permission obtained) outside clinic records
Not retained in care	Phlebotomy performed to collect viral load data	Tracking attempted at study end to ascertain missing outcomes

Laboratory and appointment data downloaded from clinical and hospital EMRs will be de-identified. Viral load results from study phlebotomy are transmitted to study staff in a secure spreadsheet. Baseline and follow-up questionnaires include validated psychosocial measures, including measures required by the funder’s cross-site data harmonization effort [41]. Study questionnaires also include questions about cell phone access and use. Study questionnaires are self-administered through Computer Assisted Survey Information Collection (CASIC), a web-based data collection tool, and have both computer-assisted personal interviewing (CAPI) and audio computer-assisted self-interviewing (ACASI) components. Outbound text messages and incoming responses from participants are captured in daily logs, as are failed attempts at SMS transmission to participants. A data manager merges all study data based on participant ID and performs periodic quality control for range and completeness of data. All participant data is stored on a secure password-protected server.

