### Statistical methods

#### Sample size

Based on clinic data [43], we designed the trial assuming a rate of virologic suppression of 60% at 12 months in the control arm. To detect an improvement of 15% in the intervention arm with 80% power and a two-sided α = 0.05, we calculated that we would need 152 participants per arm (or, 167 participants per arm assuming 90% 12-month study retention, based on the experience of other studies using the same population). Clinic data from 2013 demonstrated that at least 552 unique patients would be eligible for the study by viral load and primary care visit criteria. This calculation underestimates the actual pool of eligible patients because it excludes those who lack a viral load measurement within 28 days prior to a primary care visit. Based on trial experience during the first nine months of recruitment, we expect that approximately 10% of patients will be ineligible due to cell phone criteria and another 10% will decline participation. Given a planned accrual period of 21 months, we anticipate that the pool of eligible patients is sufficient to satisfy the target of sample size of 304.

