#### Analysis plan

Summary statistics will be used to compare study arms descriptively with respect to baseline socio-demographic characteristics and risk factors for the outcome (e.g. new to clinic vs. poorly retained; newly diagnosed vs. not). In addition, mean duration of study follow-up will be compared by arm, and process measures (e.g. rate of response to Type 2 and 3 messages, self-reported interruptions in cell phone service) will be described.

Following the intention to treat principle, participants will be analyzed in the arms to which they were randomly allocated. Virologic suppression will be analyzed using generalized estimating equation log-binomial models [44],[45] to estimate 12 month mean (95% CI) prevalence by arm and relative risk between arms, adjusted for the stratification factor (newly diagnosed in past 12 months vs. earlier), while accounting for correlation among clustered binary responses at 6 and 12 month follow up. As described in Table 2, virologic suppression status will be missing only if the participant is both lost to the clinic and to the study during the specified data collection window. Model extensions will determine the explanatory effects on virologic suppression of 1) retention in care as a mediator of effect, and 2) intensity of SMS exposure (per protocol analysis).

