## Discussion

This study protocol describes a randomized controlled trial designed to improve retention in care and virologic suppression among patients in a U.S. safety-net HIV clinic through an informational, motivational, and supportive text messaging intervention. There are several unique features of the trial that are worth highlighting. First, we sought to develop a text message intervention that could easily be replicated and deployed in a clinic setting without requiring additional staffing, as opposed to other SMS interventions that require in-person follow up of text communication. Second, to increase generalizability, the intervention is clinic-wide, rather than focused on a specific demographic or risk factor sub-group. As such, one of the challenges in designing the intervention was creating text messages that appealed to the clinic population at large. For example, in our formative focus groups, participants who used illicit substances wanted messages about substance use while those who did not use substances or who had been sober for long periods of time did not want any substance use messages. A similar phenomenon was observed with regard to spiritual and religious content. This finding helped us focus the content domains. A third unique feature of the study is that it does not provide cell phones or airtime. While this aspect of the study also increases its generalizability, we acknowledge that cell phone service interruption is common and can reduce intervention exposure. Accordingly, we will supplement the primary intent to treat analysis with per protocol analyses that adjust for intervention exposure. These trial features enable the opportunity to study intervention delivery, as well as associated barriers and costs, in a “real world” context.

One of the key elements in the success of any text messaging trial is partnering with a vendor who can accommodate control and intervention assignments, immediately troubleshoot technical glitches, and securely manage the relationship between phone numbers and de-identified study IDs. The use of pilot participants to test our text messaging protocols allowed us to realize early on that our first vendor did not have the capacity to execute the study as envisioned and to contract with a new vendor.

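### Adjusting the suppression model for SMS exposure can show a dose-response when the texts do nothing, and the mediation model states no control of mediator-outcome confounding

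*Protocol article*

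**What the plan says.** The Abstract assigns GEE log-binomial models to the intention-to-treat, per-protocol and mediation analyses alike. The Analysis plan names the stratification factor as the only adjustment in the suppression model. It then lists two extensions meant to explain suppression: "retention in care as a mediator of effect" and "intensity of SMS exposure (per protocol analysis". The Discussion describes the second as a supplement: "we will supplement the primary intent to treat analysis with per protocol analyses that adjust for intervention exposure". The reason it gives is that phone service is often interrupted.

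The article does not define the exposure variable for that model. Four sources could supply it:

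- **Replies to Type 2 and 3 messages.** Under C4C intervention, the text after Table 1 says at least one such message goes out each week because "we track responses to estimate the amount of intervention participants receive". The control condition contains no such messages.
- **Replies to the monthly check-in**, in both arms (Process outcomes).
- **Self-reported loss of phone access** (Process outcomes).
- **Daily message logs.** Data collection and management says outbound messages and incoming replies are logged, "as are failed attempts at SMS transmission to participants".

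For retention, the Analysis plan computes indicators for each 6-month period and also whole-trial indicators. It does not say which version enters the mediation model. The GEE for suppression uses the 6- and 12-month responses.

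**The concern.** Exposure and retention both arise after randomisation, so a model that conditions on either no longer compares randomised groups. A participant who answers texts is plausibly also one who takes medication and keeps appointments. If replying is entered as dose, that shared tendency is credited to the texts. In the control arm the variable is zero by design, so nothing there offsets the bias.

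Replying is also only a proxy for receipt, because a message that was read but not answered is not captured. The measures that do not depend on replying do not remove the problem. The article itself attributes disruption to lost or stolen phones, unpaid bills and loss to follow-up, each of which could plausibly predict suppression.

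The mediation model raises a different issue. If the arm changes retention, and retention and suppression share causes that are not adjusted for, the split into direct and indirect effects is biased.

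The stake is interpretation. These analyses accompany the intention-to-treat result and would carry most weight if that result were null.

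**Working it through.** **Inputs from the plan (Sample size).** Control suppression: "a rate of virologic suppression of 60% at 12 months in the control arm". Design: "To detect an improvement of 15% in the intervention arm with 80% power and a two-sided α = 0.05". Size: "we would need 152 participants per arm".

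**Reproducing the plan's figure.** With pooled variance, n = [z₀.₉₇₅·√(2p̄q̄) + z₀.₈₀·√(p₁q₁ + p₂q₂)]² / d², where p₁ = 0.60, p₂ = 0.75, p̄ = 0.675 and d = 0.15.

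- 1.960 × √0.43875 = 1.298
- 0.842 × √0.4275 = 0.550
- (1.298 + 0.550)² / 0.0225 ≈ 152 per arm, and power at 152 is 80.0%.

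The stated size is reproduced and is not in dispute. It sets the scale for the simulation.

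**Simulation of the exposure term.** 2,000 trials, 152 per arm, suppression 60% in both arms, so the intervention does nothing. The following are assumptions, because the article gives no figures for them:

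- A latent engagement trait acts on suppression and on replying with the same odds ratio (OR) per SD, varied from 1.0 to 3.0.
- Independent noise is added to replying.
- Mean reply rate is about 50%, over 52 weekly Type 2/3 prompts.

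The model is log(risk) = a + b·arm + c·(arm × reply rate), with robust standard errors. It is a modified Poisson model on the 12-month outcome, standing in for the log-binomial GEE, without the stratification factor. Entries are RR, with the share of trials rejecting at 5%:

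| OR per SD | ITT | Reply rate 0→100% | Arm term, same model | ≥50% repliers vs all controls |
|---|---|---|---|---|
| 1.0 | 1.00 (5.8%) | 1.00 (5.2%) | 1.00 (5.4%) | 1.00 (5.8%) |
| 1.5 | 1.00 (5.2%) | 1.29 (14%) | 0.88 (9%) | 1.05 (8%) |
| 2.0 | 1.01 (5.4%) | 1.76 (55%) | 0.75 (35%) | 1.11 (21%) |
| 3.0 | 1.01 (5.4%) | 2.56 (97%) | 0.61 (79%) | 1.21 (52%) |

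The arm term compares non-repliers with all controls, so it drops below 1 as the reply term rises. The two roughly cancel at the mean reply rate: 0.882 × √1.286 = 1.00, 0.748 × √1.76 = 0.99, 0.607 × √2.556 = 0.97. The model is re-sorting intervention participants by engagement, with no effect underneath.

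Comparing the arms among high check-in responders gave RR 1.00 with 5–6% rejection. Check-ins exist in both arms, and check-in replying was assumed unaffected by arm.

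**Simulation of the mediation model.** Same set-up, with binary retention driven by the same trait and assumed at 50% in controls. Results are for OR 1.5 / 2.0 / 3.0.

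- *Arm does not change retention:* retention RR 1.07 / 1.17 / 1.38, rejected in 10% / 39% / 93%. The arm RR stays at 1.00 (4–5%), so no false effect of the intervention appears.
- *Arm raises retention by an assumed 15 points, and retention has no causal effect:* retention RR 1.07 / 1.18 / 1.40. The direct-effect RR falls from its true value of 1 to 0.99 / 0.98 / 0.95. With a true total RR of 1, the implied false indirect RR is 1/0.993 = 1.01, 1/0.979 = 1.02 and 1/0.954 = 1.05.

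**The case against.** The strongest reply is that much of this is undefined rather than wrong. An article may leave the definition of exposure and the list of confounders to a fuller document that is not shown. Several parts of this reply stand.

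- A reader might infer that the exposure variable is certainly reply-based and confined to one arm. The article does not say so. Replies are the only measure it links to amount received, but other measures exist, and the stated motive of service interruption is neither reply-based nor specific to one arm.
- A reader might infer that one-way messages count for nothing. The weekly Type 2/3 message is better read as an imperfect weekly proxy for the whole stream.
- A reader might infer that the mediator is wrongly timed. That would be true only if whole-trial retention were combined with 6-month suppression in the GEE, since part of the mediator would then follow the outcome. Period-level retention is also planned, and the version used is not stated.
- A reader might carry the dose-response argument over to mediation. The simulation does not support that: with no arm effect on retention, no mediated effect arises.
- The magnitudes rest on assumed confounding and reply rates. The reply model also produces an apparent harm in its arm term, which a careful analyst might notice.

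The reply does not dispose of the central point. Adjusting the outcome model for exposure is the announced method, not a missing detail, and only the stratification factor is named for adjustment. Phone loss or failed messages entered as a dose term would be open to the same kind of confounding. Only a comparison that keeps randomisation, or explicit confounding assumptions, would answer it.

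**Conclusion.** The concern holds for the supplementary analyses, in limited form. A reply-based dose term can produce an RR of about 1.3 to 2.6 from no to full exposure with no true effect, falsely significant in 14% to 97% of trials for an assumed engagement odds ratio of 1.5 to 3.0 per SD. The bias disappears if replying and suppression share no cause. How large it would be in this trial cannot be known from the article.

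The mediation problem is separate and, in these runs, smaller. Without control of shared causes, the direct effect moved by about 1% to 5% when the arm changed retention. The retention coefficient itself can look strong without being causal.

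It would be tempting to conclude that the trial's main conclusion is at risk. It is not: the primary intention-to-treat analysis does not use these variables, and its simulated error stayed near 5%. The change is a worthwhile, inexpensive improvement to secondary evidence.

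**What to change.** 1. Replace the exposure-adjusted per-protocol model with a complier-average (instrumental-variable) estimate. Use randomised arm as instrument and the fraction of intervention messages delivered (sent minus failed, from the daily logs) as exposure, which is zero in controls. In its simplest form the estimate is (intervention risk − control risk) / f, where f is the mean delivered fraction in the intervention arm. With no effect the numerator centres on zero, so engagement alone cannot create a signal.
2. State that delivery only approximates receipt. A message to a lost or stolen phone may not be logged as failed.
3. Report reply rates descriptively, within the intervention arm only.
4. For mediation, use months 0–6 retention, already computed, as mediator of month-12 suppression. Adjust for baseline confounders such as baseline viral load, entry route (new to clinic or poorly retained) and prior missed visits, and state the no-unmeasured-confounding assumption.
5. Label both analyses exploratory and soften the claim that they will settle what explains suppression.

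The cost is a change of wording and some programming on data already being collected. The complier estimate has a wider interval, by roughly 1/f. It assumes that assignment acts only through delivered messages and, with a fractional exposure, that the effect is proportional to the amount delivered. The exclusion assumption deserves a comment, because under SMS interactions with participants the follow-up call after a missed check-in is waived for some intervention participants but not for controls.

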### Inclusion criteria

HIV-infectedAge 18 or olderEnglish-speakingAble to give informed consentHave a cell phone, can read a text message, and willing to send/receive up to 25 text messages per monthViral load >200 copies/μL within past 4 weeks and either: 1) new to clinic (no more than 2 primary care visits at Ward 86) or 2) history of poor retention (one or more missed visits at Ward 86 or lack of six-month visit constancy in the past 12 months).

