### Study procedures

#### Recruitment

A daily EMR query allows a research assistant to identify patients who may qualify for the study and remind providers that a particular patient may be eligible. Clinic providers introduce the study to patients and refer interested individuals to a research assistant. While explaining the study in more detail, the research assistant asks the patient to read a sample text message, enabling a brief literacy check. The research assistant assesses an individual’s visit history in the EMR and uses a checklist to complete screening with the patient. If individuals do not have viral load results or results pending in the EMR within the past four weeks, they can undergo phlebotomy through the study. Once eligibility is confirmed, individuals are scheduled to visit a community-based research site located in the Tenderloin neighborhood, where many patients reside, in order to complete informed consent, a baseline questionnaire, phone activation in the vendor platform, and randomization. To facilitate this visit, the research assistants offer same-day baseline study appointments and a bus token. Participants are reimbursed $30 cash for their time after completing baseline, 6 and 12 month study visits. They are not given phones nor are they compensated for any costs associated with the messages. If individuals are interested in the study but do not own a cell phone, research assistants refer them to the federal Assurance Wireless program, which assists low-income individuals in obtaining cell phones (http://www.assurancewireless.com/Public/Welcome.aspx).

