#### Randomization

At the baseline study visit, a research assistant reviews and confirms eligibility in a study database. Following written consent, a computer program captures the enrollment time and uses unpredictable specific digits to allocate patients 1:1 to study arms. Equal allocation occurs within levels of the stratification factor (HIV diagnosis within the past 12 months vs. greater than 12 months). We stratified by this factor because the estimated virologic suppression rate for individuals newly diagnosed with HIV infection in San Francisco is higher than national averages and may exceed the rate among individuals with longer standing HIV diagnoses [42]. In addition, to maximize allocation concealment and ensure balanced allocation throughout accrual, equal allocation also occurs within randomly generated blocks of size 4, 6 or 8.

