A log-binomial model will also be used to estimate 12-month mean (95% CI) visit adherence rate by arm and the relative rate between arms, adjusted for the stratification factor and correlation among responses per participant. Like the virologic suppression outcome, the ordinal retention in care outcome will be evaluated for each 6-month study period. For each participant, two indicators per period will be calculated: all scheduled primary care appointments were kept (true/false) and some scheduled primary care appointments were kept (true/false). At the end of the trial, the data will be further reduced to two indicators: all scheduled primary care appointments kept in both periods or some scheduled primary care appointments kept in both periods. Trial-level outcomes will be analyzed using an ordinal logistic regression model to estimate threshold-specific mean (95% CI) odds of retention in HIV care by arm and odds ratios between arms, adjusted for the stratification factor and number of scheduled study visits. If model diagnostics indicate that the proportional odds assumption does not hold, each threshold (all kept vs. fewer than all kept; some/all kept vs. none kept) will be modeled via a logistic regression model. A model extension will analyze study period-level outcomes.

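### Both key secondary retention models leave out entry route and prior attendance, which are known at screening; the analyses stay valid but give up some efficiency

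*Protocol article*

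**What the plan says.** The Analysis plan names the adjustment set of each retention model. The ordinal logistic model for the three-level retention variable gives "odds ratios between arms, adjusted for the stratification factor and number of scheduled study visits". The log-binomial model for visit adherence gives "the relative rate between arms, adjusted for the stratification factor and correlation among responses per participant". No other baseline variable enters either model.

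Randomisation uses one stratum: "Equal allocation occurs within levels of the stratification factor (HIV diagnosis within the past 12 months vs. greater than 12 months".

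Under Inclusion criteria a patient enters by one of two routes: "new to clinic (no more than 2 primary care visits at Ward 86" or "history of poor retention (one or more missed visits at Ward 86 or lack of six-month visit constancy in the past 12 months". Recruitment describes how this is checked: "The research assistant assesses an individual’s visit history in the EMR and uses a checklist to complete screening with the patient".

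The opening of the Analysis plan lists entry route among "risk factors for the outcome (e.g. new to clinic vs. poorly retained; newly diagnosed vs. not", but uses it only to describe the arms.

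**The concern.** The ordinal outcome is built from missed visits and six-month visit constancy. The same two quantities, measured over the year before enrolment, decide whether an established patient is eligible. The trial therefore holds a baseline counterpart of its own outcome for established patients, and knows the entry route of everyone, yet the outcome models use neither. The one baseline factor they do use, time since diagnosis, is justified under Randomization by its relation to virologic suppression; no reason is given for expecting it to predict attendance.

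Retention is the key secondary objective and the proposed mediator of the primary effect. The sample size was set on suppression and no power is stated for retention, so efficiency in these models matters. Participants differ widely: some are new, some missed a single visit, and some lacked six-month constancy. If that variation predicts later attendance, leaving it out makes a true effect harder to detect.

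**Working it through.** **1. The plan's own figure.** Sample size gives 60% vs 75%, 80% power, two-sided 0.05. With pooled variance and no continuity correction:

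n = [1.96·√(2 × 0.675 × 0.325) + 0.842·√(0.60 × 0.40 + 0.75 × 0.25)]² / 0.15² ≈ 152 per arm.

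This reproduces the stated 152 (304 in total). It concerns suppression. Nothing equivalent is given for retention, so everything below rests on assumed effects and assumed prognostic strength.

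**2. Chance imbalance.** For a binary baseline factor with prevalence p and 152 per arm, the SD of the between-arm difference is √(2p(1−p)/152).

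| p | SD | 95% range | Chance of a gap above 10 points |
|---|---|---|---|
| 0.2 | 0.0459 | ±9.0 points | 2.9% |
| 0.3 | 0.0526 | ±10.3 points | 5.7% |
| 0.5 | 0.0574 | ±11.2 points | 8.1% |

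This is ordinary random variation. It is already part of the variance of the unadjusted estimate and does not bias it.

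**3. Ordinal model.** Simulation of 1,000 trials per setting, 152 per arm, treatment odds ratio 1.8, proportional-odds outcome, likelihood-ratio test, both models fitted to the same data. The cut points put the control arm at about 30%, 45% and 25% low, moderate and high at the covariate mean. The binary covariate has 40% prevalence.

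| Covariate | Prognostic OR | Power unadjusted | Power adjusted |
|---|---|---|---|
| Binary | 1.5 | 75.8% | 76.4% |
| Binary | 2 | 77.9% | 78.5% |
| Binary | 3 | 73.8% | 77.3% |
| Binary | 5 | 70.2% | 77.3% |
| Continuous, per SD | 1.5 | 76.4% | 77.6% |
| Continuous, per SD | 2 | 72.2% | 77.3% |
| Continuous, per SD | 3 | 61.8% | 75.1% |
| Continuous, per SD | 5 | 50.2% | 69.5% |

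The gain does not come from a smaller standard error. For the binary factor with OR 3 the mean log odds ratio moves from 0.551 to 0.588 and its SE from 0.216 to 0.218, so the ratio rises from 0.551/0.216 = 2.55 to 0.588/0.218 = 2.70. The adjusted model estimates a more conditional odds ratio, which lies further from 1. Under no effect (prognostic OR 3), rejection was 5.4% unadjusted and 5.6% adjusted for the binary covariate, and 5.3% and 4.8% for the continuous one.

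A second simulation (600 trials per setting, 304 patients, 30% new to clinic with no usable history, treatment log odds ratio 0.60 to 0.78) gave, by observed correlation between past and later attendance: zero, 78.8% to 78.8%; 0.25, 82.0% to 83.5%; 0.38, 79.5% to 86.8%; 0.47, 78.0% to 88.8%.

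**4. Visit-adherence model.** Simulation of 400 trials per setting: 304 patients, 30% new, 3 to 7 visits each, every established patient given at least one past miss, log link with robust SE.

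| Correlation | SE | Power |
|---|---|---|
| 0.16 | – | 79.7%, unchanged |
| 0.35 | 0.0523 to 0.0497 | 73.8% to 77.2% |
| 0.54 | 0.0576 to 0.0510 | 71.3% to 81.5% |

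Here the SE does fall: (0.0497/0.0523)² = 0.90 and (0.0510/0.0576)² = 0.78, a variance cut of about 10% and 22%. Null rejection was 4.3% and 3.7% for the two models, so not inflated.

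**The case against.** The strongest reply is that nothing here is wrong. Adjusting for the sole stratification factor is standard and valid, type I error is held either way, and the arms will be compared descriptively on entry route, so a marked imbalance would be seen. That stands. A reader might infer that the retention comparison is biased or unsound because past attendance is neither balanced nor adjusted for. The documents do not support that: randomisation makes imbalance a matter of chance, which adds variance.

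A reader might also expect the usual linear-model gain, variance multiplied by 1 − ρ². That rule does not describe these models, and in the ordinal model the SE of the odds ratio does not shrink at all.

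Other points stand in part:

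- The size is assumed throughout. Exclusion criteria remove patients with no missed visits and full constancy, which narrows the range of prior attendance and tends to weaken its correlation with the outcome. A negligible gain cannot be ruled out. The simulation in step 4 imposed the at-least-one-miss restriction and still showed gains at correlations of 0.35 and above.
- The phrase naming entry route as a risk factor comes just before the suppression analysis and may refer to that outcome. It is supporting evidence only. The stronger ground is that the eligibility definition and the retention outcome use the same quantities.
- Newly diagnosed patients cannot have a long history at an HIV clinic, so the stratum overlaps partly with being new to clinic. It does not separate established patients from one another.
- A simple proportion of visits kept is undefined for established patients with nothing scheduled, and the two routes can overlap. Both need a rule.

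The ordinal model also adjusts for the number of scheduled study visits. That is not prior attendance. If it means appointments scheduled during follow-up, it is measured after randomisation and cannot stand in for a baseline covariate.

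**Conclusion.** The point holds as a missed efficiency gain on the key secondary outcomes. Both covariate sets are stated, both omit entry route and prior attendance, and the information is reviewed at screening. The loss is power in the ordinal model, and precision and power in the visit-adherence model.

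The size depends on a correlation that the article does not give. If past attendance is weakly prognostic the gain is about 0 to 2 points of power. If it is moderately to strongly prognostic the gain is roughly 3 to 10 points. The larger gains in the table, 13.3 points (61.8% to 75.1%) and 19.3 points (50.2% to 69.5%), need an odds ratio of 3 to 5 per SD and should not be counted on in a population selected on this variable. All figures assume 304 analysed patients and the treatment effects shown.

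**What to change.** In the Analysis plan, prespecify these baseline covariates for the visit-adherence model, the ordinal model and its separate-threshold fallback:

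1. Entry route, new to clinic or established with poor retention, with a rule that anyone with no more than 2 prior primary care visits is classed as new, even if a visit was also missed.
2. For established patients, attendance over the 12 months before enrolment, taken from the medical record and coded in categories that include a level for no scheduled visits. Set it to a constant for new patients, so that the entry-route term carries them.

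Fix the coding before outcome data are seen. Report each model with its covariates as currently planned as a sensitivity analysis. If only one covariate is added, use entry route, which is known for everyone, though its gain alone may be small: 0.6 points in the simulation at an odds ratio of 1.5 or 2.

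The cost is a wording change and one extract of records already consulted at screening, with no added patients, visits or staff. The downsides are a few more parameters, a more conditional odds ratio to interpret in the ordinal model, and a possible convergence check for the log-binomial model.
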